**Table 8. BICRO subscales**

| Subscale               | Number of items |
|-------------------------------|------------------------|
| Personal care                 | 6                      |
| Mobility                      | 6                      |
| Self-organisation             | 6                      |
| Contact with partner/children | 2                      |
| Contact with parents/siblings | 3                      |
| Socialising                   | 6                      |
| Productive employment         | 4                      |
| Psychological well-being      | 6                      |

### **5.10 Subarachnoid Haemorrhage Outcomes Tool**

The Subarachnoid Haemorrhage Outcomes Tool (SAHOT) is recorded at Day 28, 90 and 180. days and consists of 56 questions scored 0 for ‘No change’, 1 for ‘Some change’ and 2 for ‘Large or severe change’. The only possible exception is the ‘Quality of relationship with those closest’ question, which, if the subsequent question indicates the relationship is better, will be scored as 0 regardless of the response.

The sum of the scores across all 56 questions is calculated to give a raw total score and depending on the outcome corresponds to a SAHOT category (Table 9), which be analysed statistically. If the patient has died prior to the timepoint they are assigned to the worst category of 9.

**Table 9. SAHOT categories**

| Raw score | SAHOT category |
|------------------|-----------------------|
| 0–7              | 1 (best outcome)      |
| 8–17             | 2                     |
| 18–29            | 3                     |
| 30–42            | 4                     |
| 43–56            | 5                     |
| 57–73            | 6                     |
| 74–89            | 7                     |
| 90–112           | 8                     |
| Not applicable   | 9 (death)             |

If less than 50% of the 56 questions are either not completed or no questions are completed in a subscale, the data will not be included in the analysis for that patient at that timepoint. Otherwise, the raw score will be scaled up prior to assigning the SAHOT category as follows:

$$\text{Scaled raw score} = \sum_{j=1}^3 \frac{1}{p_j} \sum_{i=1}^{n_j} x_i$$

where  $x_i$  represents the individual question score for the  $n_j$  recorded answers in the  $j^{\text{th}}$  subscale and  $p_j$  represents the proportion of intended questions answered for the  $j^{\text{th}}$  subscale.

This approach will ensure that if missing data predominates in one subscale it is not under-represented in the scaled raw score. A response of 'NA' will count as a completed response.

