4. The Physical Health and Mental Health Scores are then calculated by multiplying the respective Physical Health and Mental Health Sum by 10 and adding 50 to the product. A patient with responses typical of a general population will have a score of 50 and perfect health would correspond to Physical Health and Mental Health Scores of 57.87 and 62.14 respectively.

Whilst reference means for a US population are to be applied it has been shown that their application to a UK population gives nearly identical results for the Physical Health and Mental Health Score compared to the use of UK specific reference means.

Any patient who has died before the respective timepoint will be assigned a 0 recoded score for each item of the SF-36 prior to deriving the Physical Health and Mental Health Scores.

If less than 50% of the SF-36 questions are completed at a given timepoint or no responses are completed for an individual subscale, the SF-36 data will not be included in the analysis for that patient at that timepoint. If  $\geq 50\%$  of the SF-36 questions are completed, the mean of the observed individual item recorded scores within the respective subscales will be applied to the algorithm.

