## 5.9 BICRO-39

The Brain Injury Community Rehabilitation Outcomes Scale (BICRO-39) is recorded at 90 and 180 days and consists of 39 questions scored from 0= the most favourable response (no help or prompts, once a week or more, most or all days, several hours a day, more than 20 hours a week, never - as appropriate) to 5=the least favourable response (don’t do at all, not applicable or never, almost always – as appropriate). The BICRO-39 is divided into 8 subscales as presented in Table 8. The subscale score is calculated as the mean of the individual scores within that subscale.

An overall score will also be calculated as the mean score across the 34 individual scores that are not included in the contact with partner/children and contact with parents/siblings subscales. These scales are excluded as the desirable direction may vary between patients; some patients may wish to be less reliant on carers if they are relatives and in others alienation from family member maybe a problem^6.

Any patient who has died before the respective timepoint will be assigned a subscale and an overall score of 5 corresponding to the worst outcome. If less than 50% of the 39 questions are completed at a given timepoint, or no questions have been answered in one of the 6 subscales contributing to the overall score, none of the BICRO-39 data will be included in the analysis at that timepoint. Otherwise, if ≥50% but less than 100% of the BICRO-39 questions are completed, the mean of the recorded scores within the respective subscales will be used in the analysis of subscales. However in this case, the overall score will be calculated as a weighted average of the individual subscale scores with weights of 6/34 for all subscales included apart from productive employment which receives a weight of 4/34. This approach ensures that if missing data predominates in one subscale its contribution is not down-weighted in the overall score.

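### The SAHOT completeness rule in SAP Section 5.10 is inverted: read literally, it drops well-completed forms and keeps only those at least half blank

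*SAP*

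**What the plan says.** SAP Section 5.10 describes SAHOT as a 56-item instrument with each item scored 0, 1 or 2. For scoring it states: "The sum of the scores across all 56 questions is calculated to give a raw total score". That total is mapped to categories 1 to 8 in Table 9, and patients who have died are placed in category 9.

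The completeness rule follows Table 9. Its condition is "If less than 50% of the 56 questions are either not completed or no questions are completed in a subscale", and its consequence is "the data will not be included in the analysis for that patient at that timepoint. Otherwise, the raw score will be scaled up". Scaling divides each subscale's total by the proportion of that subscale's questions that were answered, over three subscales. The stated purpose is: "This approach will ensure that if missing data predominates in one subscale it is not under-represented in the scaled raw score". An answer of NA counts as completed.

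The other multi-item questionnaires have rules of the same kind:
- SF-36 (Section 5.7) excludes on this condition: "If less than 50% of the SF-36 questions are completed at a given timepoint or no responses are completed for an individual subscale".
- BICRO-39 (Section 5.9) excludes on this condition: "If less than 50% of the 39 questions are completed at a given timepoint". It also excludes if any of the six subscales contributing to the overall score is empty.
- CLCE-24 (Section 5.8) likewise excludes when under half of its questions are completed.

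Table 11 lists SAHOT category at Days 28, 90 and 180 for formal analysis. Section 6.5 assigns it a proportional odds model.

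**The concern.** The SAHOT condition attaches the 50% threshold to questions that are *not* completed, and meeting the condition means exclusion. The better a form is filled in, the more surely it meets the condition. SF-36, CLCE-24 and BICRO-39 attach the same threshold to questions that *are* completed, so SAHOT runs in the opposite direction to all three.

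The sentence is not background text. It decides who enters a formally analysed, disease-specific outcome at three timepoints. If it were programmed as written, the analysis set would consist of deaths plus survivors who left at least half the questionnaire blank, and the patients with the most information would be removed. If it is not programmed as written, someone departs from a final SAP on an evaluability rule. Section 1 requires changes made after database lock and unblinding to be documented and fully justified in the study report, so the correction is better made before then.

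**Working it through.** The plan gives no figure to reproduce here. The check is to apply the rule to every possible number of unanswered questions.

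**Inputs (SAP Section 5.10):** 56 questions; a 50% threshold; three subscales; exclusion if the condition is met, otherwise scaling.

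**Threshold:** 0.50 × 56 = 28 questions.

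Let *m* be the number of unanswered questions, from 0 to 56.

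- Literal rule: exclude if *m*/56 < 0.5, so exclude if *m* ≤ 27.
- Rule in the form used for the other instruments: exclude if (56 − *m*)/56 < 0.5, so exclude if *m* ≥ 29.

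| Unanswered | Answered | Literal rule | Rule as for SF-36, CLCE-24, BICRO-39 |
|---|---|---|---|
| 0 (complete form) | 56 | excluded | kept |
| 1–27 | 29–55 | excluded | kept |
| 28 | 28 | kept | kept |
| 29–56 | 0–27 | kept | excluded |

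On the 50% criterion the two rules agree only at exactly 28 unanswered. Every other count is classified oppositely.

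**Second limb.** The empty-subscale condition is not inverted and works the same way under both readings. It also keeps the scaling formula defined, because an empty subscale would give a proportion answered of zero. With three subscales, a kept form needs at least 3 answers. So the literal rule as a whole keeps only forms with 3 to 28 answered questions and no empty subscale, that is, 28 to 53 unanswered.

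**Consistency with the rest of the section:**
- The scoring rule sums all 56 questions, so complete forms are meant to be scored. The literal rule excludes every complete form from a surviving patient.
- Scaling is there to repair partial missingness. Under the literal rule it would be applied only to forms at least half blank.
- Counting NA as completed makes sense only if completion favours inclusion. Under the literal rule it would push a patient towards exclusion.

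All three point to the same intended rule, and no other section of the SAP restates or corrects the SAHOT wording.

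**The case against.** The strongest reply is that this is a slip of the pen. The sentence does not parse cleanly, any reader has to repair it, and the document allows only one sensible repair. An implausible loss of SAHOT data would also be noticed. Section 6.7 calls for missing-data diagnostics if more than 15% of patients lack SAHOT data in either arm at Day 180, and the count of missing patients would then be reported. On this view the realistic outcome is a query to the statistician.

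Most of that stands. The intent can be inferred, and the error probably would be caught. But inferring the intent means overriding the written rule, and the written rule is what programming and quality control work from. The reply shows that the repair is easy; it does not show that the text is right.

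It is also fair that the reach is limited. Section 6.3 names mRS and GOSE at 90 days as the key secondary endpoints, and SAHOT is not among them. Section 6.2 has it analysed initially only in the per-protocol population.

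A reader might infer more than the SAP supports in two respects.

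- *That every retained form would be scaled up at least two-fold.* The SAP does not give the subscale sizes, and scaling is done within subscales. Assume subscales of 40, 8 and 8 questions with 12, 8 and 8 answered (28 of 56). The multipliers are 40/12 = 3.33, 8/8 = 1 and 8/8 = 1, a simple mean of (3.33 + 1 + 1)/3 = 1.78. If all the points came from the two fully answered subscales, the scaled score would equal the raw score.
- *That nearly all SAHOT data would in fact be lost.* That depends on completion rates, which the SAP does not give, and on the sentence being programmed literally.

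**Conclusion.** The rule is wrong as written. Read literally, it excludes surviving patients with 29 to 56 of 56 questions answered, including every fully completed form. It keeps only forms with 28 or more unanswered that have at least one answer in each subscale. This contradicts the scoring rule in Section 5.10 and the parallel rules in Sections 5.7, 5.8 and 5.9.

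The counts follow from the 56 items and the 50% threshold alone and need no outside assumption. The share of patients affected cannot be computed from the SAP. If every survivor answered at least 29 questions, which is an assumption, only deaths would remain at that timepoint. All would be in category 9, and there would be nothing to compare.

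The effect is confined to the SAHOT secondary analyses at Days 28, 90 and 180. The primary TCD endpoint and the key secondary endpoints, mRS and GOSE at 90 days, do not use this rule. It is best regarded as an evident drafting error in an operative derivation rule, to be corrected before unblinding, and not as a deliberate choice of analysis.

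**What to change.** Reword the condition in Section 5.10 so that a patient's SAHOT data are left out at a timepoint when less than 50% of the 56 questions are completed (fewer than 28), or when no question is completed in a subscale. The threshold then applies to completed questions, as in Sections 5.7, 5.8 and 5.9, and the empty-subscale limb stays as it is. Forms with 28 to 56 answers and no empty subscale are then kept, and complete forms are scored as the section intends.

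The cost is one sentence, with a matching check that the SAHOT derivation program follows the corrected rule. The scaling formula, Table 9, the model and the timepoints do not change for this purpose.

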### **5.11 Length of acute hospital stay**

The length of the acute hospital stay will be defined as the date of discharge (as recorded on the DISCHARG CRF) – date of ictus+1. Patients who die prior to discharge from tertiary care will be censored one day longer than the longest observed stay in either treatment group. If any patient has yet to be discharged at the time of the data cut-off they will be censored at the data cut-off date minus date of ictus+1.

A sensitivity analysis will be performed by setting the censored date of discharge at the date of death for patients who die prior to discharge.

Discharge location will be summarised only and not subject to formal statistical analysis.

### **5.12 MRI Susceptibility Weighted Imaging**

These data will be summarised separately from the CSR.

### **5.13 Safety Data**

Recording of AEs starts from informed consent and continues until at least 30 days post last dose. The definition of AEs and SAEs are given in the protocol.

Adverse events starting on or after the first treatment dose are therefore defined as Treatment Emergent Adverse Events (TEAEs). Any AE that starts more than 30 days past last dose and is considered to be at least possibly related to study treatment should also be defined as a TEAE. Any event starting before the first dose of study drug is identified as a Pre-Treatment Adverse Event (PTAE). Any event starting before the first dose of study drug that subsequently worsens is also be defined as a TEAE.

All events are coded using the MedDRA dictionary. The actual description of the AE is matched, as closely as possible, with the Lower Level Term in the dictionary.

All AEs are classified as described in Table 10.

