### 3 Study Design

The study is a randomised, double-blind, parallel-group design comparing SFX-01 (300 mg bd) administered for up to 28 days versus Placebo control in 90 patients who meet the per-protocol criteria for efficacy analyses, who have had a SAH and are referred to neurosurgical units for tertiary care.

Treatment is taken twice-daily either orally or via nasogastric tube (NG). For the first 20 patients, treatment duration is determined by the length of time spent in tertiary care (up to Day 28 post ictus). Following a DSMB review (as per protocol) for all subsequent patients the intended treatment duration is 28 days regardless of whether they remain in tertiary care for the full 28-day period. After treatment all patients are then followed up at discharge from the neurosurgical unit and then subsequently on Day 28, Day 90 and Day 180 post ictus.

A separate and more detailed investigation (sub-study) of the pharmacokinetic properties of SFN parent drug, and the primary metabolite, both in CSF and blood is also undertaken. This will involve up to 12 patients who have an External Ventricular Drain (EVD) fitted as part of their normal standard of care and is undertaken on two separate occasions within the first 7 days post ictus.

The protocol was amended part way through recruitment to stratify the randomisation by WFNS score (1-3 v 4-5) and centre.

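### The TEAE definition in SAP 5.13 omits the 30-day upper limit that its next sentence presupposes, so late unrelated AEs count as treatment-emergent if the text is applied literally

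*SAP*

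**What the plan says.** The relevant text is in SAP section 5.13, Safety Data, in this order.

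- Collection: "Recording of AEs starts from informed consent and continues until at least 30 days post last dose".
- Main TEAE rule: "Adverse events starting on or after the first treatment dose are therefore defined as Treatment Emergent Adverse Events (TEAEs").
- Late-event rule, the sentence directly after it, which adds to the TEAEs: "Any AE that starts more than 30 days past last dose and is considered to be at least possibly related to study treatment".
- Events that start before the first dose are PTAEs, and those that later worsen are TEAEs as well.

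Section 5.13 also counts an AE as drug-related if it is rated certain, probable or possible, and tabulates a missing rating as related. In Table 10 the only remaining category is unlikely, and that is what unrelated means below.

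On timing, section 3 has patients "followed up at discharge from the neurosurgical unit and then subsequently on Day 28, Day 90 and Day 180 post ictus". Section 4 brings all available safety data into the final analysis, six months after the last randomisation. Section 2 lists the safety of up to 28 days of dosing first among the primary objectives. In section 7, the overview and five of the seven listed AE tables use the TEAE flag.

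**The concern.** The main rule and the late-event rule do not fit together as written. The late-event rule singles out onset beyond 30 days and asks about relatedness. That is worth doing only if an unrelated event at that distance is not a TEAE, yet the main rule has already made every event after first dose a TEAE.

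A programmer who codes the main rule as written will count an unlikely-related complication months after dosing as treatment-emergent. One who infers the limit from the next sentence will not. The same database then gives two sets of TEAE tables for the first-listed primary objective, and the SAP does not say which is right.

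**Working it through.** The SAP gives no figure on this point to reproduce, so the check is a comparison of the two readings, followed by a calendar calculation.

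**1. The readings as sets.** Let A be onset on or after first dose. Let B be onset more than 30 days after last dose and at least possibly related.

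- Literal reading: A or B. Every event in B is already in A, so A or B = A. The late-event rule adds nothing and relatedness is never consulted.
- Bounded reading: onset from first dose to last dose + 30 days, or B. Relatedness now decides late events.

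With last dose assumed on Day 28, the limit is Day 28 + 30 = Day 58:

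| Onset | Related? | Literal | Bounded |
|---|---|---|---|
| Day 20 | No | TEAE | TEAE |
| Day 20 | Yes | TEAE | TEAE |
| Day 58 | No | TEAE | TEAE |
| Day 58 | Yes | TEAE | TEAE |
| Day 59 | No | TEAE | not TEAE |
| Day 59 | Yes | TEAE | TEAE |
| Day 150 | No | TEAE | not TEAE |
| Day 150 | Yes | TEAE | TEAE |

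The readings differ only for unrelated events starting more than 30 days after last dose.

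**2. Whether the rest of the SAP supplies the limit.**

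- The collection sentence in 5.13 gives a minimum duration, so it caps nothing.
- The rest of 5.13 and the adverse-event part of section 7 give no cut-off.
- The wording points both ways. In 5.13, *therefore* and *also* suggest a bounded window. In section 7, the table of all serious AEs is described as taking in pre-dose events, with no mention of late unrelated ones as a further difference from serious TEAEs.
- Only PTAEs and TEAEs are named as categories. On the bounded reading, a late unrelated non-serious AE has no category and no summary table.

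**3. Which outputs can move.**

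- Can change: the overview, TEAEs by preferred term, TEAEs by maximum severity, and the serious TEAE table and listing.
- Cannot change: drug-related TEAEs, because related events are TEAEs on both readings.
- Should not change: TEAEs leading to discontinuation, since treatment has already stopped before a late event starts.
- Do not use the disputed boundary: PTAEs, all serious AEs and deaths.

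The tables count patients with at least one event. A late event therefore moves a preferred-term count only if the patient had no earlier TEAE in that term, and moves the severity table only if it also raises the patient's worst grade.

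**4. How much calendar time is in dispute.** Inputs: follow-up to Day 180 (section 3); Day 180 visit window of 28 days either side (section 5.15); first dose on Day 2 (assumed).

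- Last dose Day 28 (assumed): limit Day 58. First dose to limit is 58 − 2 + 1 = 57 days; first dose to Day 180 is 180 − 2 + 1 = 179 days. Difference 179 − 57 = 122 days, and 122/179 = 68%. If the last visit falls on Day 180 + 28 = Day 208, the disputed time is 208 − 58 = 150 days.
- Last dose Day 7 (assumed): limit Day 37. Bounded window 37 − 2 + 1 = 36 days; difference 179 − 36 = 143 days, and 143/179 = 80%. An early last dose is possible in the initial cohort: "For the first 20 patients, treatment duration is determined by the length of time spent in tertiary care (up to Day 28 post ictus").

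These are lengths of time. They become events only if unrelated AEs are recorded throughout, which the SAP does not state.

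**The case against.** The strongest reply is that the paragraph can be read coherently. *Therefore* ties the TEAE sentence to the collection window just before it, and *also* introduces an extension. On that view the rule is all AEs from first dose to 30 days after last dose, plus later related ones. This is probably what was meant, and it stands as evidence of intent. It does not close the gap, because the collection window is a minimum and the limit is never written.

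A second reply also stands: the practical effect depends on AE collection after 30 days, which a protocol commonly settles and which is not visible here. Visits at Day 90 and Day 180 do not show that unrelated AEs are solicited at them.

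Four stronger readings are tempting and should not be drawn.

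- A reader might infer that the two sentences contradict each other. They do not: both can be true, and on the literal reading the second is redundant.
- A reader might infer that a primary safety analysis is distorted. The SAP names none. Safety is a primary objective, the primary endpoint is maximum post-dose MCA mean flow velocity (section 6.3), and Table 11 contains no formal test of AEs.
- A reader might infer that counts depend on how long each site kept recording. Nothing in the SAP describes such variation.
- A reader might take the windows of 57 and 179 days (a ratio of 3.1) as the inflation in TEAEs. They are calendar lengths, not event or patient ratios, and no event rates are given from which dilution of a treatment difference could be calculated.

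Late unrelated serious cases also stay visible either way, through the all-serious-AE table and the separate reporting of deaths.

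**Conclusion.** The point holds as a misstated rule with a bounded effect. As written, the definition gives a result that its own next sentence indicates was not intended: a recorded unrelated AE starting more than 30 days after last dose is a TEAE, and the relatedness condition never operates. The reach is limited to the outputs identified above as able to change.

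The size in patients cannot be stated. If unrelated AEs are not recorded beyond 30 days, the two readings give the same tables. If they are recorded to Day 180, the disputed period is 122 days for an assumed last dose on Day 28 and 143 days for an assumed last dose on Day 7. The point still merits correction because the flag underlies most AE output for the first-listed primary objective, and because a choice left open until the data are unblinded could be influenced by them.

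**What to change.** Before unblinding, put the limit into the main rule. Suggested wording: *An AE is treatment-emergent if its onset is on or after the first dose and no later than 30 days after the last dose, or if its onset is later and it is rated at least possibly related.* Name later unrelated AEs as post-treatment AEs, tabulate or list them separately, and keep them in the all-serious-AE and death outputs.

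If no limit is meant, delete the 30-day sentence instead; that also makes the section consistent.

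The cost is one clause in section 5.13, one condition in the TEAE flag and one small extra display. The downside of the bounded version is that late unrelated events leave the TEAE tables and must be read in their own display. If unblinding has already happened, section 1 provides for documenting and justifying the choice in the CSR.
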